#### Justification and summary of relevant studies

Prevalence surveys suggest that acute malnutrition affects approximately 7.5% of the world’s children under 5 years of age, with approximately 34 million children affected by MAM and 16 million children affected by SAM [^[[1]](#endnote-1)^]. Acute malnutrition is a continuum condition, but SAM and MAM are treated separately, with different protocols and therapeutic products managed by separate United Nations agencies. Although children with MAM are three times more likely to die than well-nourished children [^[[2]](#endnote-2)^], many nutrition programs offer treatment only of SAM due to resource and logistical constraints and the challenges of coordinating two separate programs.

There is global consensus around the use of Ready to Use Therapeutic Food (RUTF) for the treatment of SAM, but the treatment of MAM still lacks globally-accepted guidance. There have been many studies testing the efficacy or effectiveness of different products and supplements for the treatment of MAM, but the focus in MAM research has remained largely product-based with MAM regarded as a separate condition from SAM. The addition of milk protein to Ready to Use Supplementary Food (RUSF) appears to improve long-term outcome. A paper by Chang et al (2013) evaluating different products for the treatment of MAM demonstrated that sustained recovery was significantly more likely in those treated with soy + whey (RUSF) compared to either soy RUSF or corn-soy blend (CSB)++[^[[3]](#endnote-3)^]. During a 12-month follow-up period, only 63% of cured children remained well-nourished, 17% relapsed to MAM, 10% developed SAM, 4% died and 7% were lost to follow-up. Children treated with soy/whey RUSF were more likely to remain well-nourished (67%) than those treated with CSB++ (62%) or soy RUSF (59%) (P=0.01). RUTF for the treatment of children with SAM includes milk protein. Treating MAM with RUTF would provide MAM children with a high quality nutritional supplement, while reducing the logistics and cost of procuring a second product and managing a separate program for supplementary feeding.

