## Outcomes

Table 6: Primary and Secondary Outcomes

|  | **Measurement variable** | **Analysis metric** | **Method of aggregation** | **Time point** |
| --- | --- | --- | --- | --- |
| Primary | | | | |
| Recovery | MUAC ≥125mm and no oedema  Note: The definition of recovery in both the control and intervention groups will be defined as two consecutive measurements with a MUAC≥125mm and no oedema. For the purposes of analysis, children receiving the standard protocol will be considered as cured when their MUAC≥125mm and no oedema for two consecutive measurements, even if they continue to receive treatment until they reach a WHZ >-2. | Final value | Proportion | End of treatment |
| Secondary | | | | |
| Coverage | % of children eligible for treatment (MUAC<125mm) who receive it  Note: The coverage surveys will be based on a MUAC-only definition of Global Acute Malnutrition (GAM (MUAC<125mm). Weight and height measurements will not be taken. | Final value | Proportion | Semi-quantitative evaluation of access and coverage (SQUEAC) survey (after final enrolment) |
| Defaulter | Child discharged as defaulter (3 missed visits) | Final value | Proportion | End of treatment |
| Died | Child died during treatment | Final value | Proportion | End of treatment |
| Length of stay | Days in treatment | Duration of time | Sum | End of treatment |
| Average daily weight gain | grams/kilograms/day | Daily | Mean | End of treatment |
| Average daily MUAC gain | mm/day | Daily | Mean | End of treatment |

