## Recruitment

Prior to randomization of health facilities to either the control or intervention group, community health workers will conduct a sensitization campaign across the communities that fall within the catchment area of the 12 facilities in each country. The goal of the campaign will be to meet with community leaders and encourage them to send malnourished children to the clinics for treatment. Randomization of the facilities will occur prior to the start of the trainings of the field teams, as research officers will only be trained on the protocol they are to implement. Screening to detect malnourished cases will take place after the randomization, since referral of children to the facilities cannot begin until the teams are trained and in place and ready to provide services. Community health workers will conduct screenings in an equivalent manner across the catchment areas of both arms of the study. All malnourished children (i.e. MUAC <125mm) will receive a referral slip and their caretaker will receive instructions on how to access treatment. For any medically complicated cases requiring immediate treatment, IRC/ACF will provide transportation to the nearest stabilization center.

Patients who present to health facilities on their own will also be screened for inclusion. Weight and height measurements will be taken at the health facility only (in addition ot MUAC measurements), per national and international guidelines. All patients eligible to participate in the study based on the inclusion and exclusion criteria will be invited to enrol in the study.

In Nairobi, Kenya in 2015 the average monthly enrolment at each health facility of children classified with acute malnutrition according to the primary study definition of <125mm MUAC is 30. It is expected it will take four months to reach the sample size in Nairobi.

In Aweil East, South Sudan in 2015 the average monthly enrolment at each health facility of children classified with acute malnutrition according to the study definition of <125mm MUAC is 80. It is expected it will take two months to reach the sample size in Aweil East.

Using the above averages, enrolment is expected to take a minimum of four months, with an additional 4 months for completion of treatment of the last enrolled child. Therefore the study is expected to take 8 months.

Enrolment will occur over a period when malnutrition tends to be at its highest.

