# Methods: Data collection, management, and analysis

## Data collection methods

### 18a Plans for assessment and collection of outcome, baseline, and other trial data

A dedicated research officer will be based at each health facility for the entire duration of the study. All research officers will be given a two week training prior to study inception. They will be required to pass an exam after training is complete to test protocol knowledge, anthropometric measurement techniques (weight, height, and MUAC measurements and oedema assessment), data management techniques and coaching and counselling methodologies.

Each research officer will oversee the training and supervision of health facility staff, enrolment and treatment of children according to the study protocol and data management. S/he will conduct initial and refresher trainings with health facility staff as well as have continuous on the job trainings. They will assess the accuracy of anthropometric measurements taken by health facility staff and review the patient cards and registers on a daily basis to ensure data quality.

The information below will be collected in addition to the patient cards used in each country. MoH OTP cards will be used for all participants in the Combined Protocol. MoH OTP or SFP cards (as applicable) will be used for all participants in the Standard Protocol. Forms will be pilot tested and where needed adjusted prior to the start of the main study.

1. **Admission** (in addition to the patient card)

- Mother is caretaker (yes/no)
- Father lives in home (yes/no)
- Maternal educational achievement (none, primary, secondary)
- # children <5 in household
- Access to toilet
- Water source
- Breastfeeding in last 24 hours (yes/no)
- Livelihood/main source of income
- Other sources of free food (blanket feeding, general food distribution, etc)
- Household Hunger Score:
  - Was there ever no food to eat of any kind in your house?
  - Did you or any household member go to sleep at night and there was not enough food?
  - Did you or any household member go a whole day without eating anything at all because there was not enough food?

1. **Weekly** (in addition to the patient card) :
   - Presence of morbidity since last visit (diarrhea, vomiting, fever, cough)- *SFP*
   - Referral for medical evaluation since last visit
   - Breastfeeding in last 24 hours (yes/no)
2. **Discharge** (in addition to the patient card)
   - Breastfeeding in last 24 hours (yes/no)

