## Confidentiality

Personal information (child’s name, address and age and a unique ID) will be included in the database housed at field level until treatment is complete and all data cross-checked. Name, address and age will be removed from the database before analysis, with only the unique ID remaining. Only co-investigators (those listed as part of the research team) will have access to the database.

No personal information will be shared for research purposes. The list of personal information will be used solely to track children for counselling to ensure completion of treatment, and to ensure data quality. After the close of the study and before final analysis all personal information will be deleted.

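### Nothing is recorded after discharge and a returning child can be enrolled as new, so relapse and later death would go unseen in both arms

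*Protocol*

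**What the plan says.** **Outcomes.** In section 12, Table 6, recovery, default, death, length of stay and both gain measures are timed at the end of treatment. Only coverage has another time point. Death is "Child died during treatment". For recovery, "The definition of recovery in both the control and intervention groups will be defined as two consecutive measurements with a MUAC≥125mm and no oedema". Control children count as cured "even if they continue to receive treatment until they reach a WHZ >-2".

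**Data collection.** Section 18a lists forms at admission, weekly and at discharge, then a coverage survey and a qualitative study. None follows a discharged child. Sections 20b and 21 have the Trial Safety Committee review deaths and hospitalisations at mid-point, but no procedure collects those that occur after discharge.

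**Entry.** Section 15: "All patients eligible to participate in the study based on the inclusion and exclusion criteria will be invited to enrol in the study". The exclusions in Table 1 (section 10) concern MUAC, appetite and medical complications, not earlier participation. Section 13 speaks of new patients, but only to separate them from children already in treatment when the study opens.

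**Rationale.** Section 6a prefers milk-containing products partly because of sustained recovery, citing a study of children treated for MAM: "only 63% of cured children remained well-nourished, 17% relapsed to MAM, 10% developed SAM, 4% died and 7% were lost to follow-up".

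**Identifiers and staff.** Section 19 gives each patient a unique identifier. Under section 25, personal information "will be included in the database housed at field level until treatment is complete and all data cross-checked". Section 18a adds: "A dedicated research officer will be based at each health facility for the entire duration of the study".

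**The concern.** The trial asks whether a simplified protocol cures children as well as standard care, and its own background says that cure is often not durable. The arms differ in how soon a child may leave and in whether treatment can continue after the child is scored as cured. Early relapse is therefore a plausible place for the protocols to differ, and it lies beyond the last measurement. If the child comes back during enrolment, nothing marks the visit as a relapse. It becomes a fresh admission and may end as a second recovered record for the same child. A non-inferiority conclusion would then rest on recovery at exit, with no information on what followed, although staff at the same facilities could have recorded part of it.

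**Working it through.** **1. The plan's own figures.** Section 14 uses 85% recovery in both arms, a 10-point margin, 80% power, two-sided 5% and an ICC of 0.05.
- Per arm before clustering: (1.960 + 0.842)² × 2 × 0.85 × 0.15 / 0.10² = 200.2, rounded up to 201.
- Design effect: 1 + 99 × 0.05 = 5.95.
- 201 × 5.95 = 1,196 per arm, or 11.96 clusters of 100. The stated 12 reproduces, and this point does not change it.
- Cited follow-up: 17 + 10 + 4 = 31%. Only the relapse part, 17 + 10 = 27%, can return. The five cited percentages add to 101 through rounding.

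**2. The arms side by side (Tables 2 to 4 and 6).**

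| | Minimum stay stated | After being scored cured |
|---|---|---|
| Combined, both countries | 3 weeks | Discharge with 7 sachets |
| Control, Kenya OTP | 2 months | Discharged to SFP; primary outcome still to be reached |
| Control, Kenya SFP | none stated | May continue until WHZ >-2 |
| Control, South Sudan OTP | none stated | Discharged to SFP; primary outcome still to be reached |
| Control, South Sudan SFP | 6 weeks | May continue until WHZ >-2 |

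The two arms can therefore differ in time to exit and in treatment after MUAC cure.

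**3. How many children could enter twice.** Assumptions: the cited 27% relapse in 12 months applies here at a constant rate, entry is uniform over a window of W months, cure comes after a stay of L months, and every relapse inside the window re-enrols. Section 15 expects W = 4 months in Nairobi and 2 in Aweil East.

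Monthly rate h = −ln(1 − 0.27)/12 = 0.0262.

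Share = 0.85 × (1/W) × [(W − L) − (1 − exp(−h(W − L)))/h].

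For W = 4 and a 3-week stay (L = 0.692): W − L = 3.308 and (1 − exp(−0.0867))/0.0262 = 3.168 (unrounded h), so the share is 0.85 × 0.139/4 = 3.0%.

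| Stay | 4-month window | per 150 children | 2-month window |
|---|---|---|---|
| 3 weeks | 3.0% | 4.4 | 0.9% |
| 6 weeks | 1.9% | 2.8 | 0.2% |
| 8 weeks | 1.3% | 1.9 | about 0% |
| 12 weeks | 0.4% | 0.6 | 0% |

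If the 27% were reached within 6 months, the 4-month figures become 5.8% at 3 weeks and 2.5% at 8 weeks. If it were reached within 3 months, an extreme case, the figure at 3 weeks is 10.9%.

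**4. Effect on the recovery rate.** A second episode enters numerator and denominator. With a share r of repeat entries in one arm only, recovering at rate q, the arm's rate moves by r/(1 + r) × (q − 0.85).
- q = 85%: no change at any r.
- q = 100%: r = 3% gives 0.03/1.03 × 15 = +0.4 points; r = 6% gives 0.06/1.06 × 15 = +0.8; r = 10.9% gives 0.109/1.109 × 15 = +1.5.
- q = 70%: r = 3% gives −0.4 points; r = 6% gives −0.8.
- q = 0, the unrealistic floor: r = 3% gives 0.03/1.03 × 85 = −2.5 points.

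The sign depends on q, about which the protocol says nothing.

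**The case against.** The case against has several parts, and much of it limits the size of the point.

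- **Scope.** The research question is programme indicators and coverage, so follow-up after discharge can be called an extra. That is fair for active follow-up. It is weaker for events that reach the same facilities while study staff are there.
- **Unseen documents.** A first-enrolment rule could sit in the statistical analysis plan, and the patient cards or questionnaires, which are not shown, may record re-admission. But an analysis plan can use only what is recorded, and outcomes and data collection are fixed in this protocol, with no rule for a returning child.
- **The arm contrast is uneven.** Kenya SFP states no minimum stay. Combined children at 115 to below 125 mm are seen bi-weekly and need two qualifying measurements, so counting visits after admission their earliest exit is week 4, as in Kenya SFP. The Combined arm gives a discharge ration and SFP lists none. This stands: a difference in relapse between arms is possible, not shown.
- **The 31% is borrowed.** It comes from MAM children on other products over 12 months. It illustrates and does not estimate anything for this SAM and MAM population.
- **Observation does not always stop at cure.** Control children kept on treatment after MUAC cure are still seen for a time. That is true, and it makes observation after cure unequal between arms.

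**Conclusion.** The point holds as a modest design weakness. No outcome or procedure covers relapse or death after discharge, and nothing bars or flags a discharged child who enrols again. A relapse is then not recorded as one, and two episodes of one child stand as two children. The effect on the recovery proportion is small: about 0.4% to 3% of enrolled children in a 4-month window and 1% or less in a 2-month window, which is under about one point on the rate unless relapse is concentrated very early or second episodes recover much less often than first ones. These figures rest on the borrowed 27%, a constant rate and full re-enrolment.

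Three stronger inferences are tempting and not supported.
- *Double entry favours the Combined Protocol.* Recovery is a proportion, and the direction is not established.
- *Linkage is impossible.* Section 25 keeps the unique ID and deletes personal information only after study close and before final analysis, so linkage is possible. It is simply not provided for.
- *The unseen events rival the margin.* Applying 31% at a constant rate (−ln(0.69)/12 = 0.0309 per month) over 2 to 5 months gives 6.0% to 14.3% of 3,600 × 0.85 = 3,060 cured children, or 184 to 438. That is a total over both arms. The 10-point margin concerns a difference between arms in recovery at exit, so the two cannot be compared.

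**What to change.** 1. Add a prior-enrolment and re-admission field to the admission form, linked to the child's existing unique ID. Check it across study facilities, since those in Nairobi lie about 3 to 5 km apart. State in section 25 that the link is kept until study end.
2. State that only a child's first enrolment counts in the recovery analysis.
3. Record any return of a discharged child to a study facility, with the measurements taken at that visit, and any known death, up to October 2017.
4. Report these by arm with time since discharge, descriptively, to the Trial Safety Committee and in the final report.

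**Cost.** One form field and a register check by research officers already on site, with no extra visits and no change to treatment. Section 23 implies an amendment to the three ethics committees, and identifiers may be held somewhat longer.

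**Downside.** Passive capture misses children who do not return or go elsewhere. It also depends on coverage and time at risk, which may differ by arm: section 7 expects higher coverage under the Combined Protocol, and earlier discharge leaves longer to observe. The report should say so and draw no formal comparison.

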## Interventions

### 11a. Interventions for each group

Table 2: Combined Protocol Intervention: Kenya and South Sudan

| **Combined Protocol** |  |
| --- | --- |
| **Admission Criteria** | <125mm MUAC  AND/OR bipedal oedema (+)  AND clinically uncomplicated (i.e. passes appetite test, no Integrated Management of Childhood Illness (IMCI) danger signs/ no serious medical complications) |
| **Treatment Frequency** | <115mm: Weekly  115-<125mm: Bi-weekly |
| **Dosage** | <115mm and/or oedema (+): Two 92g sachets RUTF/day (1000 kcal/day)  115-<125mm : One 92g sachet RUTF/day (500 kcal/day) |
| **Transition from 2 RUTF to 1 RUTF:** | Two consecutive weekly measurements at or above 115mm and no oedema |
| **Cured** | ≥125mm for 2 consecutive measurements and no oedema, with 3 week minimum stay |
| **Default** | Absent for 3 consecutive visits |
| **Non-recovered** | Has not achieved discharge criteria within 16 weeks |
| **Discharge procedures** | Discharge ration of 7 RUTF sachets |
| **Routine medical treatments (as per national protocol):** | For all children with MUAC <115mm and/or bipedal oedema (+) on admission:   - **Amoxicillin:** Give first dose at health facility and then give remainder to caretaker with instructions to give twice daily for 7 days   For all children with MUAC <125mm and/or bipedal oedema (+) on admission:   - **Malaria**: according to national protocol - **Measles:** one vaccine on 4^th^ visit (4^th^ week) (children >6 months) (unless already vaccinated) - **Deworming:** one dose (albendazole or mebendazole) on the second visit (second week) (children >1 year) |
| **Referral Procedures (as per national protocol)** | Any child who develops medical complications and/or is not responding to treatment will be referred for a medical evaluation and/or to the Stabilization Center.  ‘Not responding to treatment’ will be defined in the following way:   - Failure to gain any weight (non-oedematous children) - Failure to start to lose oedema - Oedema still present - Weight loss since admission to program (non-oedematous children) - Failure of appetite test - Weight loss of 5% of body weight - Weight loss for two successive visits |

Table 3- Standard Protocol Intervention- Kenya

| **Standard Protocol- Kenya** | **OTP** | **SFP** |
| --- | --- | --- |
| **Admission Criteria** | - WHZ < -3   And/or   - MUAC < 115mm   And/or   - Bilateral pitting oedema (+/++) | - Discharged from OTP   And/or   - WHZ <-2 to WHZ >-3  and/or - MUAC 115mm < 125mm |

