| **Treatment Frequency** | Weekly | 14 days |
| **Dosage** | RUTF 200kcal/kg/day | - Plumpy Sup (500 kcal/day) |
| **Cured** | - MUAC >115mm   And/or  WHZ >-3 Z-score  and   - No oedema for two consecutive visits   and   - Minimum two months stay | Child maintains WHZ >-2 Z-score and/or MUAC ≥125mm for a period of two consecutive weighs/measurements  *For the purposes of analysis, children will be considered ‘cured’ after reaching ≥125mm for a period of two consecutive measurements.* |
| **Default** | Absent for 3 consecutive visits | Absent for 3 consecutive visits |
| **Non-recovered** | Has not achieved discharge criteria within 4 months | Has not achieved discharge criteria within 4 months |
| **Discharge procedures** | - Give a final ration of seven sachets as a weaning off ration - Refer to SFP | N/A |
| **Routine medical treatments** | - **Amoxicillin:** Give first dose at health facility and then give remainder to caretaker with instructions to give twice daily for 7 days - **Malaria**: according to national protocol - **Measles:** one vaccine on 4^th^ visit (4^th^ week) (children >6 months) (unless already vaccinated) - **Deworming:** one dose (albendazole or mebendazole) on the second visit (second week) (children >1 year) | N/A |
| **Referral Procedures** | Any child who develops medical complications and/or is not responding to treatment will be referred for a medical evaluation and/or to the Stabilization Center.  ‘Not responding to treatment’ will be defined in the following way:   - Failure to gain any weight (non-oedematous children) - Failure to start to lose oedema - Oedema still present - Weight loss since admission to program (non-oedematous children) - Failure of appetite test - Weight loss of 5% of body weight - Weight loss for two consecutive visits | |

Table 4- Standard Protocol Intervention- South Sudan

| **Standard Protocol- South Sudan** | **OTP** | **SFP** |
| --- | --- | --- |
| **Admission Criteria** | - WHZ < -3   And/or   - MUAC < 115mm   And/or   - Bilateral pitting oedema (+ /++)   AND   - Appetite test passed - No medical complications - Child clinically well and alert | - Discharged from OTP   And/or   - WHZ <-2 to WHZ >-3 and/or - MUAC 115mm < 125mm   AND   - Appetite test passed - No medical complications - Child clinically well and alert |
| **Treatment Frequency** | Weekly | 14 days |
| **Dosage** | RUTF 200kcal/kg/day | RUSF 500 kcal/day |

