| **Cured** | Child maintains MUAC >115mm and/or WHZ >-3 and no oedema for two consecutive visits  Note: The anthropometric indicator (during admission) that is used to confirm SAM should also be used to assess whether a child has reached nutritional recovery (during discharge) | Child maintains WHZ >-2 and/or MUAC >125mm for two consecutive visits  and  6 week minimum stay  *For the purposes of analysis, children will be considered ‘cured’ after reaching ≥125mm for a period of two consecutive measurements.* |
| **Default** | Absent for 2 consecutive visits | Absent for 2 consecutive visits |
| **Non-recovered** | Has not achieved discharge criteria within 2 months | Has not achieved discharge criteria within 3 months |
| **Discharge procedures** | - Give a final ration of seven sachets as a weaning off ration - Refer to SFP | .N/A |
| **Routine medical treatments:** | - **Amoxicillin:** Give first dose at health facility and then give remainder to caretaker with instructions to give twice daily for 7 days - **Malaria**: according to national protocol - **Measles:** one vaccine on 4^th^ visit (4^th^ week) (children >6 months) (unless already vaccinated) - **Deworming:** one dose (albendazole or mebendazole) on the second visit (second week) (children >1 year) | - **Deworming:** one dose (albendazole or mebendazole) on the second visit (second week) (children >1 year) |
| **Referral Procedures** | Any child who develops medical complications and/or is not responding to treatment will be referred for a medical evaluation and/or to the Stabilization Center.  ‘Not responding to treatment’ will be defined in the following way:   - Failure to gain any weight (non-oedematous children) - Failure to start to lose oedema - Oedema still present - Weight loss since admission to program (non-oedematous children) - Failure of appetite test - Weight loss of 5% of body weight - Weight loss for two successive visits | |

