## Participant timeline

Once the study begins, all existing patients in the health facilities assigned to the intervention will complete treatment per the standard protocol, and all new patients eligible for inclusion will begin treatment per the Combined Protocol.

Enrolment: March- June 2017

SQUEAC: June 2017

Qualitative study: June 2017

End of study: October 2017

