# Methods: Monitoring

## Data monitoring

### 20a Role of Data Safety and Monitoring Board (DSMB)

It is expected the trial enrolment will be complete within 3-4 months, due to high caseloads in the catchment area of each health facility. Due to the short duration of the trial (8 months, including 4 months for completion of treatment of the last enrolled child), meaningful interim analysis by a DSMB will be difficult. However, in order to have independent oversight of the safety aspects of the trial, a Trial Safety Committee (TSC) will be formed. The TSC will comprise of an independent chair, a statistician from the LSHTM, and a health official from each country (Kenya and South Sudan).

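### Four months after the last enrolment covers the 16-week Combined course but not the longest control SAM course, and daily gain is read at exits set by different rules in each arm

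*Protocol*

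**What the plan says.** **Time after last enrolment.** Section 15 (Recruitment) expects at least four months of enrolment, "with an additional 4 months for completion of treatment of the last enrolled child", so eight months in all. Section 20a gives the same eight months, "including 4 months for completion of treatment of the last enrolled child". Section 13 sets enrolment from March to June 2017 and states "End of study: October 2017".

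**Length of a course (section 11a).**
- Combined (Table 2): a single programme. A child is non-recovered if the child "Has not achieved discharge criteria within 16 weeks".
- Kenya control (Table 3): the OTP and SFP columns each say "Has not achieved discharge criteria within 4 months". The OTP discharge procedure is "Give a final ration of seven sachets as a weaning off ration - Refer to SFP", and discharge from OTP is an SFP admission criterion.
- South Sudan control (Table 4): the OTP and SFP cells read "Has not achieved discharge criteria within 2 months | Has not achieved discharge criteria within 3 months", and OTP again refers on to SFP. Section 15 adds "It is expected it will take two months to reach the sample size in Aweil East".

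No overall limit across OTP and SFP is given.

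**Outcomes (section 12, Table 6).** Recovery is two consecutive MUAC readings of at least 125 mm without oedema, in both arms, read at end of treatment. The SFP cure cells of Tables 3 and 4 also say that, for analysis, children count as cured at two readings of at least 125 mm. Daily weight gain and daily MUAC gain are also read at end of treatment. Minimum stays are 3 weeks (Combined), two months (Kenya OTP) and 6 weeks (South Sudan SFP), and control treatment may continue until WHZ is above -2.

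**The concern.** The four-month statement fits one arm and not all of the other. Control OTP discharges at MUAC above 115 mm, while recovery needs 125 mm twice. Unless a control SAM child reaches 125 mm while still in OTP, the child has to be followed into SFP to be scored. If the study closes first, the outcome of a slow responder in that arm may not be recorded. Research officers, who enter the data, are placed for the duration of the study (sections 18a and 19), and no analysis plan can recover visits that were never entered.

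Recovery is the primary outcome of a non-inferiority trial with a 10-point margin. Its MUAC threshold is common to both arms, but the time allowed to reach it is not. The differences push in opposite directions:
- A longer control SAM window can raise control recovery.
- Closure before that window ends, and the 3-month South Sudan MAM limit, can lower it.

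The second matter concerns the denominator of daily gain. Stage 1 found that gain slows as MUAC rises (section 6a). Days spent in control treatment after the cure point therefore tend to be slow-gain days. Averaging over them can make the control arm look worse for the same response, on a measure that the section 7 hypothesis uses to judge whether the protocols are equally effective.

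**Working it through.** **1. The plan's own figure.** 4 months of enrolment + 4 months = 8 months. This reproduces, and March to October 2017 agrees with it. Taking 31 October as the latest reading of October 2017, a child enrolled on 30 June has 123 days.

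**2. Longest permitted course, for a child enrolled on 1 March.**

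| Group | Limit | Ends | Days |
| --- | --- | --- | --- |
| Control MAM, South Sudan | 3 months | 1 June | 92 |
| Combined, both countries | 16 weeks | 21 June | 112 |
| Control MAM, Kenya | 4 months | 1 July | 122 |
| Control SAM, South Sudan | 2+3 months | 1 August | 153 |
| Control SAM, Kenya | 4+4 months | 1 November | 245 |

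**3. The same limits against closure on 31 October.**
- Combined: 30 June + 112 days = 20 October. Fits. The latest enrolment date that fits is 11 July.
- Kenya control MAM: 30 June + 4 months = 30 October. Fits.
- South Sudan control SAM: 31 May + 5 months = 31 October. Fits for enrolment up to 31 May. At 80 a month, 150 per facility takes 150/80 = 1.9 months, so the expected enrolment there would finish in time.
- Kenya control SAM: 30 June + 8 months = 28 February 2018, which is 120 days after closure.
- Kenya control SAM child enrolled on 30 June who leaves OTP as cured at the two-month minimum: enters SFP on 30 August with a limit of 30 December (122 days), of which 62 days (51%) fall before 31 October.

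**4. Kenya enrolment.** Section 15 gives 30 children per facility per month and section 14 asks for 150 per facility. 30 × 4 = 120, and 150/30 = 5 months. If Kenya recruits the full 150 at that rate, enrolment ends about 31 July, and 31 July + 112 days = 20 November. In that case even the Combined course would not fit an October closure.

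**5. Daily gain: an illustration on assumed values.** A MAM child starts at 120 mm, measures at least 125 mm on day 14 and 126 mm on day 28. Under Combined the child exits on day 28. Under South Sudan SFP the 6-week minimum holds the same child to day 42.
- To day 28: 6/28 = 0.214 mm/day.
- To day 42 with no further gain: 6/42 = 0.143 mm/day, 33% lower.
- To day 42 with a further 1 mm, the most this child can have gained between days 14 and 28: 7/42 = 0.167 mm/day, 22% lower.

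More generally, if cure comes at T weeks and the child stays E more weeks at a fraction r of the earlier pace, gain to exit divided by gain to cure is (T + rE)/(T + E). For T of 6 to 12, E of 2 to 6 and r of 0 to 0.5, this runs from 6/12 = 0.50 to 13/14 = 0.93. T, E and r are assumptions, not values from the protocol.

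**The case against.** **Eight months is an extreme.** This stands. To use it, a child must take about four months to meet OTP discharge and then nearly four more in SFP. A child still failing OTP at four months is already non-recovered. A reader might infer that control SAM children generally need eight months, or that the primary result is biased in a known direction. The protocol supports neither, because it gives limits, not expected courses.

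**No enrolment date leaves room for the Kenya maximum.** A reader might infer this from the 1 November date above, but it turns on one day. By calendar months a child enrolled on 1 March overruns 31 October by a day; with an average month length the first day or two of March would fit. The safe statement is that nearly all dates, and all late ones, fall short.

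**Closure is not said to cut children off.** This is also correct. The durations are planning estimates, and the stated purpose of the tail is to complete treatment. Analysis rules for children still in treatment could sit in an analysis plan that is not shown. What remains is that the stated time is too short for its stated purpose in one group.

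**Exit rules belong to the strategies compared.** The comparator is each national protocol as delivered (section 6b), so different windows are partly the point. That justifies keeping the end-of-treatment result and programme length of stay. It does not explain why growth rate should depend on discharge rules.

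**The common cure wording may already govern gain.** Tables 3 and 4 are not worded for recovery alone, and a reader might infer that gain is certain to be computed to programme exit. The protocol does not settle this: the cure definition is not expressly applied to the gain period, while Table 6 says end of treatment.

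**Length of stay aggregated as a sum.** A reader might take this for an error. It can sensibly mean days added across OTP and SFP, so no fault is found.

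**Conclusion.** The point holds in a limited form. Four months after the last enrolment is sufficient for the Combined arm and for control MAM children. For control SAM children it is short of the permitted course by up to four months in Kenya, and by up to one month in South Sudan if enrolment there runs to the end of June. Those at risk of being unresolved at closure are Kenya control SAM children who are slow to reach 125 mm, mainly those enrolled late. How many there are, and which way the pooled recovery difference would move, cannot be derived from the protocol. This rests on the OTP and SFP limits running one after the other, which is the natural reading of two separate limits joined by a referral, and on closure no later than 31 October.

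For daily gain, the period is tied to exit rules that differ by arm and is not expressly cut at the common cure date. The effect can run against the control arm. Its size depends on the extra days spent after cure and on how far growth has slowed by then. The figures above are illustrations only.

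**What to change.** **1. Closure and recovery.** Correct the four-month statement in sections 15 and 20a so that it is not claimed to cover control SAM children. Commit to recording those children, across OTP and SFP, to at least 16 weeks from enrolment, and move closure if Kenya enrolment runs past 11 July (to 20 November if it ends on 31 July). Beside the end-of-treatment result, pre-specify recovery within 16 weeks of enrolment in both arms and both countries, with children discharged earlier as non-recovered counted as not recovered. Present this as a sensitivity analysis and state its limits. It uses the Combined arm's own cap, so later control recoveries appear only in the end-of-treatment result. It also leaves the shorter South Sudan limits (2-month OTP, 3-month SFP) in place, so it does not fully equalise the windows.

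**2. Daily gain.** In Table 6, compute daily weight and MUAC gain in both arms to the date of the second consecutive MUAC of at least 125 mm without oedema, or else to the last visit. Keep programme length of stay, as total days across OTP and SFP, as a separate outcome.

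**Cost.** A corrected statement, one added analysis and a clarified outcome definition. All use visit data already collected, and care, randomisation and sample size are unchanged. The only possible operational cost is a later closure if Kenya enrolment overruns.
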